**RESEARCH PROTOCOL ABSTRACT:**

This is an open-label Phase I/II trial to assess the feasibility and safety of combined plasma exchange (PEX), rituximab, and conventional corticosteroid administration on the outcome of hospitalized patients with acute IPF exacerbations. The specific aims of this study are:

1. To assess the feasibility and safety of combined PEX, rituximab, and conventional corticosteroid administrations for the treatment of hospitalized patients with acute IPF exacerbations by monitoring indices of respiratory (PaO2) and cardiovascular function during the treatment interval.
2. To assess the efficacy of combined PEX, rituximab, and conventional corticosteroid administrations for the treatment of hospitalized patients with acute IPF exacerbations on patient survival in comparison to historical controls. Patient survival for this investigation will be defined using the composite outcome of 60 day survival and/or survival to lung transplantation.

Subjects between 18 and 80 years of age who have a confirmed diagnosis of IPF, and meet all the study requirements will be enrolled in this study. A total of 10 subjects of both genders and all ethnic backgrounds with acute IPF exacerbations hospitalized at UPMC will be enrolled in this study.

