Idiopathic pulmonary fibrosis (IPF) is an interstitial lung disease characterized by inflammation and fibrosis of lung parenchyma affecting gas exchange. IPF has a poor prognosis with median survival of approximately 3 years from the time of diagnosis. Although IPF is chronic in nature and usually slowly progressive, some patients may experience an accelerated phase of the disease that has a very poor prognosis, with death occurring in a few days to weeks. Acute IPF exacerbation has been defined as an acute, clinically significant deterioration, without unidentified cause, of respiratory status in patients with underlying IPF. Current criteria for acute IPF exacerbations include a combination of the following that have occurred within a 30 day period: exacerbation of dyspnea and/or evidence of abnormal gas exchange, as defined by a lower partial pressure of arterial oxygen (PaO2)/percentage of inspired oxygen (FiO2) ratio or a decrease in PaO2; new bilateral radiographic opacities; and an absence of infection or another identifiable etiology such as left heart failure, or pulmonary embolism.

The etiology of IPF remains elusive,1-3 and the mechanism(s) leading to acute exacerbations of this disease are especially mysterious.4 The majority of IPF patients with acute exacerbation are admitted to intensive care units with acute respiratory failure. To date, there is no proven successful treatment for acute IPF exacerbation that has been shown to prolong survival, aside from lung transplantation. Treatment of acute IPF exacerbations traditionally has consisted of high-dose corticosteroids (pulse solumedrol), but unfortunately, many patients do not respond to treatments. During the past year, 42 patients were admitted to UPMC PUH with IPF exacerbations and the hospital mortality rate was approximately 50%. The majority of these patients died awaiting lung transplantation. Accordingly, the development and demonstration of a feasible medical treatment that prolongs short-term patient survival, could act as a bridge to transplantation. This would have a hugely beneficial effect by enabling more of these otherwise doomed patients to have the only currently recognized treatment for this disease process.

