**2.3 STUDY ENDPOINTS**

**2.3.1. The Primary End-Points**

The primary outcome measures for this study are the feasibility and safety of the regimen in patients with IPF exacerbations. Safety will be assessed by monitoring three variables of cardiopulmonary function:

- Respiratory deterioration defined as PaO2 on days 0, 3, 5, 7, 14, 28 (if still hospitalized) while breathing 100% FiO2 for >20 minutes by either endotracheal tube (ETT) or nonrebreathing face mask if not intubated (face masks and O2 delivery systems for nonintubated patients will be standardized).
- Hemodynamic deterioration defined as need for initiation of vasopressor agents, inotropes, or intravenous diuretics.

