**2.3.2. Secondary End-Points**

The secondary outcome measures a composite outcome defined as survival to 60 days or survival to transplantation at any time post therapy. Comparison will be made to historical hospital controls who had IPF exacerbations.

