**5.1.2 Potential Risks of Experimental Intervention**

Insertion of a central venous catheter for plasmapheresis:

Complications of this procedure include bleeding at the insertion site, pneumothorax, catheter-associated blood clots and infections (local and systemic). The complication rate of central vein catheters, inserted by physicians of variable experience, has been reported to be 15%.80

Plasmapheresis: The most common adverse effect is a drop in blood pressure associated with symptoms of dizziness or light-headedness79. Unusual complications include extracorporeal coagulation. The addition of citrate to the infusion solutions can lead to hypocalcemia with associated peri-oral tingling, numbness and more rarely muscle irritability, cardiac arrhythmias, and seizures.

Rare complications are infections by blood products (fresh frozen plasma (FFP)), transfusion reaction to FFP, an allergic reaction to the replacement solutions or sterilizing agents for the tubing, and adverse effects of immunosuppression produced by the associated hypogammaglobulinemia. Medications dosing may also need to be adjusted in patients being treated with plasmapheresis as certain medications can be removed by the procedure.

Rituximab:

The most common adverse effects (>10%) with rituximab from available clinical trials include74,78:

General: Fever (5% to 53%), chills (3% to 33%), headache (19%), pain (12%)

Dermatologic: Rash (1-15%), pruritus (5% to 14%), angioedema (1-11%)

Gastrointestinal: Nausea (8% to 23%), abdominal pain (2% to 14%)

Hematologic: Cytopenias (2-49%)

Neuromuscular & skeletal: Weakness (2% to 26%)

Respiratory: Cough (13%), rhinitis (3% to 12%)

Infusion Related: angioedema, bronchospasm, chills, dizziness, fever, headache, hyper-/hypotension, myalgia, nausea, pruritus, rash, rigors, urticaria, and vomiting; reactions (7-39%)

Less common adverse reactions (1% to 10%) include:

Cardiovascular: Hypotension (2-10%), peripheral edema (8%), hypertension (6% to 8%), flushing (5%), edema (<5%)

Central nervous system: Dizziness (10%), anxiety (2% to 5%), agitation (<5%), depression (<5%), hypoesthesia (<5%), insomnia (<5%), malaise (<5%), nervousness (<5%), neuritis (<5%), somnolence (<5%), vertigo (<5%), migraine (RA: 2%)

Dermatologic: Urticaria (2% to 8%)

Endocrine & metabolic: Hyperglycemia (9%), hypoglycemia (<5%), hypercholesterolemia (2%)

Gastrointestinal: Diarrhea (10%), vomiting (10%), dyspepsia (3%), anorexia (<5%), weight loss (<5%)

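### The primary safety outcome contains only PaO2 and haemodynamic support, so the regimen's own listed harms count only when they happen to move those variables

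*Protocol*

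**What the plan says.** Specific Aim 1, in the Abstract and again in 1.2, assesses feasibility and safety "by monitoring indices of respiratory (PaO2) and cardiovascular function during the treatment interval". Section 2.3.1 turns this into the primary endpoint: "Safety will be assessed by monitoring three variables of cardiopulmonary function". Two components follow. The respiratory one reads "Respiratory deterioration defined as PaO2 on days 0, 3, 5, 7, 14, 28 (if still hospitalized", measured on 100% oxygen. The other reads "Hemodynamic deterioration defined as need for initiation of vasopressor agents, inotropes, or intravenous diuretics". No adverse event category appears among them.

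Section 5.1.2 describes the risks of the intervention. For the central catheter: "Complications of this procedure include bleeding at the insertion site, pneumothorax, catheter-associated blood clots and infections (local and systemic"). For plasma exchange it names hypotension as the most common effect, then hypocalcaemia, reactions to plasma or replacement fluid, and "adverse effects of immunosuppression produced by the associated hypogammaglobulinemia". For rituximab it lists cytopenias, infusion reactions and, rarely, hepatitis B reactivation and other infections.

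Adverse events are handled elsewhere. They are documented at visits and at Day 60 (2.2.2), recorded on case report forms (5.4.2), graded and attributed (5.4.3), reviewed (5.4.4) and reported (5.4.6). Section 2.4.2 gives their only stated analysis, a Fisher or chi-square test of differences between groups. The trial is non-randomized with one prospective arm. On controls, 2.3.2 says, for the survival composite: "Comparison will be made to historical hospital controls who had IPF exacerbations".

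**The concern.** Safety is a primary question of this trial, and the definition of a primary endpoint belongs in the protocol. Two features of the definition work against it.

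First, the harms that the protocol expects from a catheter-based, immunosuppressive regimen have no place of their own in the outcome meant to answer the safety question. An infection, a bleed or a cytopenia that leaves PaO2 and haemodynamic support unchanged does not contribute.

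Second, PaO2 is hard to read as harm in this population. Section 1.3 says: "The majority of IPF patients with acute exacerbation are admitted to intensive care units with acute respiratory failure", and puts hospital mortality near 50%. The endpoint is called deterioration, yet no fall in PaO2 is specified that would count as one, and no comparison series is named. A fall cannot be assigned to treatment, and a stable value does not show that the regimen was free of harm.

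At stake is whether ten treated patients yield a usable statement about regimen harm for the larger trial that 2.4.1 says this study should inform.

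**Working it through.** The point concerns the scope of an endpoint. The protocol states no figure to reproduce, so the main check sets the sections side by side.

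**1. Which listed harms can reach the primary outcome**

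| Harm in 5.1.2 | Route into 2.3.1 |
| --- | --- |
| Hypotension (plasma exchange, rituximab) | Only if a vasopressor or inotrope is started |
| Catheter or other infection | Only if it leads to shock treated with those drugs, or lowers PaO2 |
| Pneumothorax, bronchospasm | Only if PaO2 falls at a scheduled measurement |
| Insertion-site bleeding, catheter clots | None direct |
| Cytopenias | None direct |
| Other infusion reactions (rash, fever, rigors, urticaria) | None direct |

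Section 2.3.1 announces three variables and its text lists two. A third would, by that section's own description, also be cardiopulmonary, so the table would hold.

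**2. Whether the stated adverse event analysis fills the gap**

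- 2.4.2 tests differences between groups.
- 2.1 describes a non-randomized trial, and 2.2.1 gives every subject the combined treatment.
- 2.3.2, Aim 2 and 2.4.1 name historical controls for survival only. Adverse event data from controls are not mentioned anywhere.

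The stated test therefore has no identified second group, and no single-arm estimate is stated in its place.

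**3. How readable the two components are**

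- PaO2: no threshold and no named reference series, in patients whose disease itself lowers PaO2.
- Haemodynamic support: exclusion criterion 8 in 3.3 removes subjects who already need a vasopressor, so a vasopressor start is a new event. This component is cleaner, although it too has no reference rate.

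**4. How likely the omitted events are in 10 subjects**

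Inputs: n = 10 (2.4.1); catheter complication rate 15% and rituximab infusion reactions 7% to 39% (both 5.1.2). Assuming independent subjects, P(at least one) = 1 − (1 − p)^10.

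- Catheter: expected number 10 × 0.15 = 1.5.
- Catheter, at least one: 1 − 0.85^10 = 0.80.
- Catheter, at least two: 1 − 0.85^10 − 10 × 0.15 × 0.85^9 = 0.46.
- Infusion reaction, low end: 1 − 0.93^10 = 0.52.
- Infusion reaction, high end: 1 − 0.61^10 = 0.99.

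These are events of any grade. The chance of a grade 3 or higher event is lower, and the protocol gives no rate for it.

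**5. What a single-arm count can say**

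With 0 of 10 subjects affected, the upper limit of the exact two-sided 95% interval is 1 − 0.025^(1/10) = 0.308. Even a clean result would leave a true rate of about 31% compatible with the data. The interval shows this; a between-group test without a comparator does not.

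**6. Whether the data needed are already collected**

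- Study coordinators review records for adverse events until 72 hours after the last dose (5.4.2). The last rituximab infusion is on Day 13 (2.2.1), so this ends about Day 16, some 12 days before Day 28.
- Blood counts are logged at Days 0, 7, 14 and 28, or at discharge if earlier (2.2.2).
- Day 60 is normally a telephone contact (2.2.2), which cannot grade a cytopenia.

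The visits and laboratory schedule support a window to Day 28 or discharge once record review is extended. They do not support complete grading to Day 60.

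**The case against.** The best defence is that safety is judged more widely than 2.3.1 suggests. Adverse events are documented, graded, attributed and reported to the DSMB and IRB. Blood counts, INR and liver tests are logged. Benefit and risk are reviewed periodically, and the stopping rule rests on attributable fatal or life-threatening events and not on PaO2. Tabulation by type and grade is commonly left to a statistical analysis plan, which is not at hand. All of this stands. A reader might infer from Aim 1 that the trial judges safety only by cardiopulmonary function; the protocol as a whole does not support that.

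Three further inferences also go too far. A reader might conclude that a run of catheter infections with stable PaO2 would be declared safe. The protocol sets no criterion for declaring the regimen safe, and such a run would go to the benefit-risk review in 5.4.3 and 5.4.4. A reader might say that the outcome misses the listed harms altogether, but treated hypotension, septic shock and pneumothorax can reach it. And a reader might say that it mainly tracks the exacerbation. That is a reasonable inference for PaO2, although no figure in the protocol shows it; it is weaker for haemodynamic support.

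The quoted rates are also open to challenge. The 15% applies to operators of variable experience, whereas 5.5.2 plans trained staff and ultrasound guidance. The infusion rates come from other trials, and 5.5.2 expects premedication to lessen general reactions.

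The defence does not answer the point about endpoint scope. Monitoring and reporting are not an endpoint. The timed reports in 5.4.6 are limited to unexpected events, and 5.4.5 requires the investigator to think a serious event study-related. The one analysis that the protocol does state for adverse events lacks an identified comparator.

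**Conclusion.** The point holds as one of endpoint definition. The primary safety outcome includes no adverse event category; the harms in 5.1.2 enter only through PaO2 or haemodynamic support. The only stated adverse event analysis does not fit a single prospective arm. PaO2, without a threshold or reference, cannot separate regimen harm from disease; the haemodynamic component is better placed to do so.

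On size, the protocol's own rates make at least one catheter complication (0.80) or infusion reaction (0.52 to 0.99) likely among 10 subjects. These figures assume independent subjects and rates carried over from other settings at any grade. They show that such events are likely enough to deserve a place in the outcome; they do not predict severe events in this trial. The change should be made because it bears on the trial's primary question. It does not imply that patients go unmonitored.

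**What to change.** 1. In 2.3.1 and Aim 1, add a primary safety variable: the number of the 10 subjects with at least one treatment-emergent infection, bleeding event, thrombosis, pneumothorax, cytopenia or infusion reaction of grade 3 or higher on the 5.4.3 scale, from Day 0 through Day 28 or discharge. Report it with an exact 95% CI, and state beside it how many subjects died or were discharged before Day 28.
2. In 2.4.2, replace the between-group adverse event test with this single-arm estimate.
3. Report events learned at the Day 60 contact separately.
4. Reconcile the 72-hour record-review limit in 5.4.2 with the Day 28 window.
5. Optional: if control charts are reviewed for survival, abstract vasopressor, inotrope and intravenous diuretic starts from the same charts as a descriptive reference. The protocol describes no such chart review, so this should not be assumed to be free.

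Cost: wording changes in the two places where safety is defined and in 2.4.2, plus about 12 more days of record review for subjects still in hospital. The reported primary safety result will look less favourable, and with 10 subjects the interval will be wide. Clinical management does not change.

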**STUDY PRINCIPAL INVESTIGATORS:**

**Principal Investigator: [name]**

**Co-Principal Investigator: [name]; [name]**

**SECTION 1 – STUDY OBJECTIVE, SPECIFIC AIMS, BACKGROUND, AND SIGNIFICANCE**

- 1. **OBJECTIVE**

The goal of this open-label Phase I/II clinical trial is to assess the feasibility, safety and preliminary comparison of efficacy of combined plasma exchange (PEX), rituximab, and conventional corticosteroid administration on the survival of patients with acute IPF exacerbations in comparison to historical controls.

Heretofore, most patients who develop acute exacerbations of IPF succumb to the lung disease within days to a few weeks. Current, conventional treatment using high, albeit unspecified, doses of corticosteroids seem to have no therapeutic efficacy. Lung transplantation is believed to be an effective treatment for IPF, but many patients with the acute manifestation of this disease who are referred to UPMC die before their lung transplantation evaluations are complete, and/or before a suitable donor lung can be procured.

We have recently found evidence that pathogenic processes leading to IPF progression appear to be mediated by autoantibodies. Very analogous autoimmune responses are also involved in some cases of chronic lung allograft rejection and other acute lung injuries (ALI), including adult respiratory distress syndrome (ARDS) associated with polymyositis and other conventional autoimmune syndromes. As is the case with IPF, neither chronic allograft rejection nor the other autoantibody-mediated ALI syndromes respond to corticosteroids or other simple, nonspecific immunosuppressive agents. However, treatments that specifically reduce autoantibody production (e.g., rituximab) and/or remove pre-existent autoantibodies (e.g., plasma exchange [PEX]) appear to be more efficacious, and have even rescued critically ill patients with severe respiratory failure who did not respond to conventional steroid-based regimens.

We hypothesize that acute IPF is a manifestation of autoantibody-mediated lung injury, and that mechanistically-focused treatments will have better efficacy than nonspecific, current standard medical therapy. We further anticipate that our rituximab + PEX treatment will result in improved short-term mortality of IPF patients with acute exacerbations, enabling many more of them to survive long enough for definitive lung transplantation. As such, the experimental treatment proposed here will be a beneficial “bridge” to “buy time” for these otherwise doomed patients to benefit from curative lung transplantation.

- 1. **SPECIFIC AIMS**

1. To assess the feasibility and safety of combined PEX, rituximab, and conventional corticosteroid administrations for the treatment of hospitalized patients with acute IPF exacerbations by monitoring indices of respiratory (PaO2) and cardiovascular function during the treatment interval.

2. To assess the efficacy of combined PEX, rituximab, and conventional corticosteroid administrations for the treatment of hospitalized patients with acute IPF exacerbations on patient survival in comparison to historical controls. Patient survival for this investigation will be defined using the composite outcome of 60d survival and/or survival to lung transplantation.

**As such, more IPF patients with acute exacerbations will live long enough to have the clinical evaluations necessary for lung transplantation and until suitable donor organs can be procured.**

We hypothesize the combined treatment will ameliorate autoantibody-mediated lung injury and have a demonstrably beneficial effect on patient outcome.

- 1. **BACKGROUND**

Idiopathic pulmonary fibrosis (IPF) is an interstitial lung disease characterized by inflammation and fibrosis of lung parenchyma affecting gas exchange. IPF has a poor prognosis with median survival of approximately 3 years from the time of diagnosis. Although IPF is chronic in nature and usually slowly progressive, some patients may experience an accelerated phase of the disease that has a very poor prognosis, with death occurring in a few days to weeks. Acute IPF exacerbation has been defined as an acute, clinically significant deterioration, without unidentified cause, of respiratory status in patients with underlying IPF. Current criteria for acute IPF exacerbations include a combination of the following that have occurred within a 30 day period: exacerbation of dyspnea and/or evidence of abnormal gas exchange, as defined by a lower partial pressure of arterial oxygen (PaO2)/percentage of inspired oxygen (FiO2) ratio or a decrease in PaO2; new bilateral radiographic opacities; and an absence of infection or another identifiable etiology such as left heart failure, or pulmonary embolism.

The etiology of IPF remains elusive,1-3 and the mechanism(s) leading to acute exacerbations of this disease are especially mysterious.4 The majority of IPF patients with acute exacerbation are admitted to intensive care units with acute respiratory failure. To date, there is no proven successful treatment for acute IPF exacerbation that has been shown to prolong survival, aside from lung transplantation. Treatment of acute IPF exacerbations traditionally has consisted of high-dose corticosteroids (pulse solumedrol), but unfortunately, many patients do not respond to treatments. During the past year, 42 patients were admitted to UPMC PUH with IPF exacerbations and the hospital mortality rate was approximately 50%. The majority of these patients died awaiting lung transplantation. Accordingly, the development and demonstration of a feasible medical treatment that prolongs short-term patient survival, could act as a bridge to transplantation. This would have a hugely beneficial effect by enabling more of these otherwise doomed patients to have the only currently recognized treatment for this disease process.

Our recent studies, and others,5-9 show the presence of aberrant immune responses in IPF patients that support an autoimmune pathogenesis, leading us to posit the central hypothesis of this proposal: Antibody-mediated autoimmunity plays an important role in IPF exacerbations.

In addition to relevant preliminary data, the plausibility of our central hypothesis is also supported by analogies to other antibody-mediated acute lung injuries (ALI). Manifestations of acute IPF exacerbations are very similar to suddendeteriorations of interstitial lung disease among myositis patients with anti-synthetase autoantibodies,10,11 and lung transplant recipients with allograft rejection due to anti-donor HLA antibodies.12 Autoantibodies against IL-8 (and other autoantigens) have also been implicated in some cases of adult respiratory distress syndrome.13,14 These syndromes all share common features of rapid pulmonary deterioration in the absence of other obvious extrinsic processes, as well as histological patterns of diffuse alveolar damage and, notably, nearly invariable refractoriness to corticosteroids.

In contrast, however, *specific treatments to remove or reduce autoantibodies are now a mainstay of therapy for anti-donor HLA antibody-mediated lung transplant rejection,13 and have also been effective in allograft recipients and other patients with acute autoantibody-mediated lung diseases who failed prior courses of corticosteroids.11,12,15*

The production of IgG antibodies (and autoantibodies) with specificity for protein determinants is the result of coordinated interactions between the three major elements of the adaptive immune system: 1.) HLA molecules; 2.) T-cells; and 3.) B-cells. In brief, highly specific peptide antigens are presented by HLA molecules of antigen presenting cells, including B-cells, to the limited pool of T-cells with antigen receptor specificity for these particular peptide-HLA complexes. In turn, these now antigen-activated “armed effector” T-cells divide, generating sometimes prodigious numbers of clonal daughter progeny that elaborate myriad mediators which directly injure tissues, and/or activate and recruit other immune effectors, including B-cells.16,17

With respect to our supportive/preliminary data to follow, all IPF clinical specimens were(and will continue to be) obtained from carefully scrutinized subjects who fulfill consensus ATS/ERS diagnostic criteria.1 Diagnoses were prospectively established by expert specialized clinicians blinded to experimental study results, who analyzed all clinical information, including medical histories and physical exams, pulmonary function tests (PFTs), laboratory studies that included serologic tests for conventional autoimmune syndromes, as well as expert rheumatologist evaluations, chest radiographs, and HRCT scans. No IPF study subject had evidence or a history of connective tissue diseases, drug toxicities, or occupational/environmental exposures associated with lung disease. All lung histology from subjects showed usual interstitial pneumonia (UIP) or end-stage fibrotic disease. Specimens from patients with clinical, histological, or microbial evidence of ongoing infections were not analyzed. Laboratory investigators were blinded to subject identities. Mann-Whitney tests were used for comparisons of unpaired continuous or ordered variables, and a Wilcoxon was used for paired tests. Dichotomous variables were compared by chi-square, and odds ratios (OR) and 95% confidence intervals (CI) established by logistic regression. Hazard ratios (HR) and CI were established by proportional hazard. Survival analyses were performed using product-limit, with comparison by log-rank. Data here are depicted as means + SEM and p values are delineated.

Our studies to date have found interrelated abnormalities of all three adaptive immune elements in IPF patients that support the central hypothesis of this proposal:

